# A multi-centre, open label, randomised, parallel-group, superiority Trial to compare the efficacy of URsodeoxycholic acid with RIFampicin in the management of women with severe early onset Intrahepatic Cholestasis of pregnancy: the TURRIFIC randomised trial

**DOI:** 10.1186/s12884-020-03481-y

**Published:** 2021-01-12

**Keywords:** Intrahepatic cholestasis of pregnancy, Cholestatic pruritus, Bile acids, Ursodeoxycholic acid, Rifampicin, Maternal and neonatal health outcomes

## Abstract

**Background:**

Severe early onset (less than 34 weeks gestation) intrahepatic cholestasis of pregnancy (ICP) affects 0.1% of pregnant women in Australia and is associated with a 3-fold increased risk of stillbirth, fetal hypoxia and compromise, spontaneous preterm birth, as well as increased frequencies of pre-eclampsia and gestational diabetes. ICP is often familial and overlaps with other cholestatic disorders.

Treatment options for ICP are not well established, although there are limited data to support the use of ursodeoxycholic acid (UDCA) to relieve pruritus, the main symptom. Rifampicin, a widely used antibiotic including in pregnant women, is effective in reducing pruritus in non-pregnancy cholestasis and has been used as a supplement to UDCA in severe ICP. Many women with ICP are electively delivered preterm, although there are no randomised data to support this approach.

**Methods:**

We have initiated an international multicentre randomised clinical trial to compare the clinical efficacy of rifampicin tablets (300 mg bd) with that of UDCA tablets (up to 2000 mg daily) in reducing pruritus in women with ICP, using visual pruritus scores as a measuring tool.

**Discussion:**

Our study will be the first to examine the outcomes of treatment specifically in the severe early onset form of ICP, comparing “standard” UDCA therapy with rifampicin, and so be able to provide for the first-time high-quality evidence for use of rifampicin in severe ICP. It will also allow an assessment of feasibility of a future trial to test whether elective early delivery in severe ICP is beneficial.

**Trial identifiers:**

Australian New Zealand Clinical Trials Registration Number (ANZCTR): 12618000332224p (29/08/2018).

HREC No: HREC/18/WCHN/36.

EudraCT number: 2018–004011-44.

IRAS: 272398.

NHMRC registration: APP1152418 and APP117853.

**Supplementary Information:**

The online version contains supplementary material available at 10.1186/s12884-020-03481-y.

## Background

Intrahepatic cholestasis of pregnancy (ICP) is the most frequent liver disorder specific to pregnancy, with an annual Australian incidence of 0.6–0.8% [1]. Its cardinal features are maternal pruritus and increased serum bile acids (BA), commonly towards the end of the third trimester. The pruritus, though often mild, can occasionally be extremely severe, causing major skin excoriations, profound sleep disturbances and associated psychopathology, with iatrogenic premature delivery for symptom relief. ICP can also cause severe liver dysfunction and jaundice. BA are formed in the liver and secreted in the bile into the intestine, where they emulsify fat in the ingested food and enable its uptake into the liver, where the BA are recycled. In ICP, this cycle of “enterohepatic circulation” is inhibited and serum BA concentrations increase, providing a marker for the disorder [2]. Increased rates of postpartum haemorrhage (PPH) reported in early studies [3] have not been confirmed in more recent larger datasets [4]. Gallstones may be present more often in these women [5]. Women with hepatitis C infection have a higher incidence of ICP [6]. Maternal symptoms typically resolve after birth, but affected women have an increased risk of hepatobiliary disease in later life [6]. There are few data for long term outcome in the children of mothers with ICP [7].

ICP has been associated with increased fetal risks, including spontaneous preterm birth, fetal hypoxia and compromise (including meconium-stained liquor) and unexpected intrauterine fetal death [3]. Higher concentrations of circulating BAs are associated with increased fetal risks, including spontaneous preterm birth, asphyxial events and stillbirth [8, 9]. Early onset (less than 34 weeks gestation) severe (defined as serum BA > 40 μmol/L) ICP is a rare disorder with an Australian incidence of 0.1% per annum [1].

The aetiology of ICP has been linked to increased concentrations of oestradiol, progesterone and, in particular, of progesterone metabolites in pregnancy, which impact the farnesoid X receptor (FXR)-mediated BA homeostasis pathways [10]. Why only some women develop ICP may be attributable to genetic variants of the genes encoding biliary transporters, eg phosphatidyl-choline floppase multidrug resistance protein 3 (MDR3; *ABCB4*), Bile Salt Export Pump (BSEP; *ABCB11*), phosphatidyl serine flippase (*ATP8B1*), the multidrug resistance-associated protein 2 (MRP2; *ABCC2*), and also tight junction protein 2 (TJP2), [11] together with FXR, which is critical in the transcriptional activation of both *ABCB11* [12] and *ABCB4* [13]. Further evaluation of genetic variants that confer ICP susceptibility may allow precision medicine in the identification of women at increased risk of adverse pregnancy outcome, and also those more likely to respond to targeted treatment of ICP with specific drugs.

A number of agents from different pharmacological classes have been used in the management of women with ICP. These include: ursodeoxycholic acid (UDCA), cholestyramine, dexamethasone, s-adenosylmethionine and, most recently, rifampicin. None are based on high level evidence and, as a consequence, there are various concerns over costs, side effects and possible harms. The publication of the PITCHES study, a placebo-controlled RCT of UDCA in 605 women with ICP of any severity recruited between 20 and 40^+ 6^ weeks gestation, has confirmed a small reduction in pruritus for UDCA but no benefit in respect of a composite of adverse perinatal outcomes [14]. Pharmacological treatment of ICP is the subject of a 2020 Systematic Review in the Cochrane Library [15]. Included in this review were 26 randomised controlled trials involving 2007 participants. The trials were mostly at moderate to high risk of bias. Compared with placebo, the pooled results showed a probable small improvement in pruritus score measured on a 100 mm visual analogue scale (VAS) (mean difference (MD) − 7.64 points, 95% confidence interval (CI) − 9.69 to − 5.60 points for UDCA in two trials (715 women) (GRADE moderate certainty). The evidence for fetal compromise and stillbirth were uncertain, due to serious limitations in study design and imprecision (risk ratio (RR) 0.70, 95% CI 0.35 to 1.40; 6 trials, 944 women; RR 0.33, 95% CI 0.08 to 1.37; 6 trials, 955 women; GRADE very low certainty).

Understanding of the mechanism of action of the various drugs is limited. Ursodeoxycholic acid (UDCA) is a naturally occurring BA, which displaces more hydrophobic endogenous bile salts from the BA pool. This action may shield the hepatocyte membrane from the damaging toxicity of bile salts, enhancing BA clearance across the placenta from the fetus [16]. UDCA has also been shown in vitro to protect rat cardiomyocytes from damage by endogenous bile salts [17].

Since the publication of the previous Cochrane review in 2013 [18], there has been increasing interest in the use of rifampicin in treating women with ICP. Rifampicin is a semisynthetic antibiotic with a wide range of antimicrobial activity and is a first-line agent for treatment of tuberculosis, including for treatment of pregnant women [19, 20]. Rifampicin has also been shown to have the capacity to reduce serum BA in the management of cholestasis outside of pregnancy. It is a pregnane X-receptor (PXR) agonist and a potent inducer of key enzymes in the hepatic and intestinal detoxification machinery (such as CYP3A4, CYP2D, UGT1A1, SULT2A1) and export pump MRP2 [21]. A systematic review of pharmacological interventions for pruritus in palliative care showed that, in patients with cholestatic pruritus, data favoured the use of rifampicin, showing a low incidence of adverse events when compared with placebo [22]. There have been no reported trials comparing UDCA and rifampicin in the treatment of pruritus in any clinical scenario. Rifampicin has no known teratogenic effects, although an effect on vitamin K metabolism mandates parenteral neonatal administration of vitamin K [23]. In a questionnaire survey of clinicians, who reported results on 27 women with 28 affected pregnancies identified via the International Obstetric Medicine forum: the clinical case notes of women with ICP treated with UDCA and rifampicin were reviewed, and data regarding maternal and perinatal outcomes were extracted [24]. While serum BA remained high whilst taking UDCA as monotherapy, use of rifampicin led to reductions in serum BA in more than half the women, and to halving of serum BA in more than 33%. No adverse effects were reported with either drug. There were no stillbirths and no postpartum haemorrhage reported, but the numbers were very small.

Data from The Netherlands suggest that rifampicin may be a more appropriate therapy for individuals with *ABCB11* mutations associated with clinical BSEP deficiency and Benign Recurrent Intrahepatic Cholestasis (BRIC) outside of pregnancy [25]. Recent data from France, on the other hand, while supporting the use of UDCA in ICP, did not show any relation of *ABCB4* mutations to treatment with UDCA [26].

Other strategies to improve outcomes for pregnant women have focussed on the timing of birth. A trial involving 62 women with ICP (any gestation or severity) compared early term delivery (induction or delivery started between 37^+ 0^ and 37^+ 6^ weeks gestation) versus expectant management (spontaneous labour awaited until 40 weeks gestation or caesarean section undertaken for normal obstetric indications, usually after 39 weeks gestation). There were no stillbirths or neonatal deaths in either group. No clear differences in caesarean section, passage of meconium-stained liquor or admission to neonatal intensive care unit were observed [27]. Despite the lack of RCT evidence to support benefit for early delivery and potential harms, many centres around the world have adopted a practice of ensuring birth for women by 37 weeks gestation, particularly of women with severe ICP, to avoid the increased risk of stillbirth [28].

We have therefore planned a series of trials to answer some of these important clinical questions, using a similar plan as the protocol for the prospective STRIDER studies [29]. In this initial study, we compare the use of rifampicin vs UDCA in women with severe early onset ICP. The trial has as its primary outcome pruritus, an important clinical endpoint for the women affected, which can be measured easily and effectively with a well-validated visual scale as a continuous variable. It also allows a much smaller sample size in a superiority design than that required to demonstrate differences in perinatal morbidity and mortality. The results of the trial will then be able to be compared, subject to HREC and local governance approval after submission of a separate protocol, data sharing agreements and appropriate de-identification of the data, in a meta-analysis with the results from the PITCHES trial to give a robust estimate of the sample size required to conduct a definitive clinical trial with serious perinatal morbidity and mortality as major outcomes.

Our study will be the first to examine the outcomes of treatment specifically in the severe early onset form of ICP, comparing “standard” UDCA therapy with rifampicin, and so be able to provide for the first-time high-quality evidence for use of rifampicin in severe ICP.

## Methods/design

### Trial hypotheses

The primary trial hypothesis is that rifampicin, compared with UDCA treatment of women with severe early onset ICP, commenced between 14^+ 0^ and 33^+ 6^ weeks of gestation, reduces the degree of pruritus, measured as worst itch in the previous 24 h assessed on a patient-recorded visual analogue scale.

Secondary trial hypotheses include:
Rifampicin, compared with UDCA, improves short-term outcomes for both mother and infant in severe early onset ICP, including the length of gestation and the incidence of caesarean section and preterm birth.Rifampicin, compared with UDCA, improves markers of maternal liver function in severe early onset ICP, including serum BA and serum transaminase concentrations.

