### Inclusion criteria

Women are considered eligible for inclusion into the trial with the following criteria:
Severe ICP (defined as pruritus with increased total serum BA ≥40 μmol/L) confirmedViable pregnancy between 14^+ 0^ and 33^+ 6^ weeks gestation inclusive (as determined by ultrasound pregnancy dating)No known lethal fetal anomalySingleton pregnancyObstetric care in a consultant-led unitAged 18 years or overWritten informed consent has been obtained

Standardisation of serum BA concentration measurements: participating units will have tested a series of serum samples sent out from Adelaide, for comparison and correlation with the Adelaide values, and subsequent adjustment of the results from the local laboratories to enable standardisation of the results across the trial. Similar quality control testing will be carried out every 12 months.

Women who present with non-severe ICP (total serum BA < 40 μmol/L) between 14^+ 0^ and 33^+ 6^ weeks gestation, and who then progress, with or without UDCA treatment, to severe ICP (total serum BA ≥40 μmol/L) prior to 34^+ 0^ weeks gestation, are eligible for entry into the trial, providing they are willing to accept random allocation to treatment (with a wash-out period of any pre-existing UDCA treatment for 4–7 days to enable baseline biochemical data to be obtained, and confirm eligibility only if serum BA were measured ≥40 μmol/L while not taking UDCA), they meet the other inclusion criteria and they do not meet any of the exclusion criteria (below), in which case they will be randomised either to rifampicin therapy or to commence/continue with UDCA therapy.

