### Secondary outcomes

The secondary short-term maternal outcomes are defined as:
Serial biochemical indices of disease: serum concentration of bile acids (BA), bilirubin (total), alanine transaminase (ALT), gamma glutamyl transferase (GGT)Peak serum concentration (between randomisation and delivery) of BAMaximum doses of trial medications required, and days of such medicationsDays from randomisation to birthDays to resolution/amelioration of symptomsNeed for added treatment with UDCA or rifampicin as appropriate after 7 days of the randomly allocated drug therapyNeed for additional therapy at maximum trial dosage (e.g. antihistamines, cholestyramine, therapeutic plasma exchange/other)Incidence of gestational diabetes mellitus (WHO criteria) and its treatment (diet/metformin/insulin), and of gestational hypertension/pre-eclampsia (ISSHP criteria)Upper abdominal ultrasound/biliary pathologyMode of onset of labour, and gestation at onsetTiming of steroids (if any) for fetal pulmonary maturationDuration of labourPresence of meconium in the liquor intrapartumGestation at birthMode of birth, classified as spontaneous vaginal, instrumental vaginal or CaesareanReason for induction or pre-labour Caesarean sectionEstimated blood loss at birthTime for resolution of symptoms after birth

The secondary short-term perinatal outcomes are defined as:

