### Baseline assessments

Baseline data, including all demography, itch chart results, serum BA concentrations, other serum analytes, viral serology and coagulation profiles, including prothrombin time and activated partial thromboplastin time (recorded within 7 days prior to randomisation, and 4–7 days after cessation of any previously initiated UDCA therapy), are entered on the web-based data base. The itch chart is a previously validated 100 mm visual analogue score where the participant is asked to score her worst itch in the previous 24 h [27]. All laboratory data are measured in the routine hospital laboratories for each centre.

Other biological samples, including serum, urine, faeces, liquor and placenta, may also be collected (with participant consent) under separate protocols and stored for later assessment.

On completion of these details, the database issues a randomisation notification to the site PI/delegate. A prescription for the allocated study treatment is written by the local PI or their delegate, using a standard clinical prescribing script, and the participant collects the study treatment from the pharmacy.

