### Biological samples and laboratory tests

Routine biochemical, autoimmune and viral serology, and coagulation testing as per local maternity unit guidelines (commonly serum BA, liver biochemistry, including ALT/GGT/bilirubin, viral serology including hepatitis A, B, C, D, E and G (as per local guidelines), cytomegalovirus (CMV), Epstein-Barr virus (EBV) and herpes simplex (HSV), autoimmune liver serology (mitochondrial, smooth muscle, ANA and LKM antibodies) and INR/APTT).

Serum BA do not need to be collected fasting but should be collected shortly before the next scheduled dose of UDCA, if being taken. Fasting/non-fasting and the length of time since the last dose of UDCA should be noted.

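### Secondary hypothesis 2 counts lower serum bile acids as better liver function on rifampicin, but the comparator is itself a bile acid and no UDCA-free measure is defined

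*Protocol article*

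**What the plan says.** Under Trial hypotheses, the protocol article states as a directional secondary hypothesis that rifampicin, compared with UDCA, "improves markers of maternal liver function in severe early onset ICP, including serum BA and serum transaminase concentrations".

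The Secondary outcomes list includes "Serial biochemical indices of disease: serum concentration of bile acids (BA), bilirubin (total), alanine transaminase (ALT), gamma glutamyl transferase (GGT"), peak serum BA between randomisation and delivery, and cord blood BA.

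On the comparator, the Background says: "Ursodeoxycholic acid (UDCA) is a naturally occurring BA, which displaces more hydrophobic endogenous bile salts from the BA pool".

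On measurement, Baseline assessments says: "All laboratory data are measured in the routine hospital laboratories for each centre". The word total is attached to BA only in the eligibility text, for example "Severe ICP (defined as pruritus with increased total serum BA". No assay is named and no UDCA-free fraction is defined.

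Three provisions bear on UDCA and the BA value:
- Women already on UDCA enter "with a wash-out period of any pre-existing UDCA treatment for 4–7 days to enable baseline biochemical data to be obtained", and eligibility then depends on a value obtained "while not taking UDCA".
- Follow-up BA samples "should be collected shortly before the next scheduled dose of UDCA, if being taken", with the time since the last dose recorded.
- Under Subsequent visits, appropriate biochemical samples are taken before the other trial drug is added, so that comparisons can be made.

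Data analysis adjusts comparisons for stratification variables and, where relevant, the baseline value. It leaves further detail to a separate analysis plan.

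**The concern.** A marker used to compare two drugs should not contain one of them. If the laboratory value sums all bile acids, a woman taking UDCA has the comparator counted in her result, while a woman on rifampicin alone does not. The counting error runs one way, towards the stated hypothesis.

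At stake is what the trial may conclude about the liver. A lower BA value on rifampicin could reflect better bile-acid handling, or only the absence of UDCA from the sample, and the article gives no means of telling these apart. The hypothesis and its direction are fixed in the article, so a later analysis plan would not necessarily repair this.

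**Working it through.** The article gives no figure for this effect, so there is nothing to reproduce. The check sets the provisions side by side and then shows what the size would depend on.

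**1. Does each provision remove UDCA from the between-arm comparison?**

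| Provision | What it does | What remains |
|---|---|---|
| Wash-out of 4–7 days before baseline | Makes baseline and eligibility values off-drug | Follow-up in the UDCA arm is on-drug |
| Adjustment for baseline | Removes baseline imbalance | Cannot correct a component that appears only after baseline, in one arm |
| Sampling shortly before the next dose | Lowers the drug's share | Dosing is once or twice daily and continues to birth, so the sample is a trough and not drug-free |
| Time since last dose noted | Documents exposure | No use of it is stated |
| Inter-laboratory standardisation | Aligns local values with the coordinating laboratory | Separation of bile-acid species is not described |
| Sampling before an add-on drug | Gives values before UDCA enters the rifampicin arm | UDCA in its own arm is unaffected |

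**2. What sets the size?**

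Notation:
- E is the BA level in the rifampicin arm (no UDCA).
- d is the fraction by which UDCA displaces endogenous BA in its own arm.
- f is the share of the UDCA arm's measured value that is UDCA.

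Measured value in the UDCA arm = E(1 − d)/(1 − f).

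The documents give neither d nor f, so both are assumptions. E is set at the eligibility threshold of 40 μmol/L for illustration.

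- No displacement (d = 0), the largest effect for any given f: f = 10% gives 40/0.9 = 44; f = 30% gives 40/0.7 = 57; f = 50% gives 40/0.5 = 80 μmol/L.
- Partial displacement, f = 30% and d = 15%: 40 × 0.85/0.7 = 49 μmol/L.
- Displacement equal to the share, f = d = 30%: 40 × 0.7/0.7 = 40 μmol/L, so no difference appears.

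In the last case the value would hide a 30% fall in non-UDCA bile acids on UDCA. The unfractionated value still does not measure what the hypothesis needs.

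**3. What could it do to a test? (upper-bound illustration, d = 0)**

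Inputs: the planned 54 per arm less 5% drop-out is 54 × 0.95 ≈ 51; two-sided alpha is 0.05; equal endogenous BA in both arms; assumed standard deviation s of log BA from 0.5 to 0.9.

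Chance of a significant result favouring rifampicin = Φ(−ln(1 − f)/(s√(2/51)) − 1.96).

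- f = 0: 2.5%, the nominal value.
- f = 10%: −ln 0.9 = 0.105. With s = 0.5 the standard error is 0.099 and the chance is 19%; with s = 0.9 it is 0.178 and the chance is 9%.
- f = 30%: −ln 0.7 = 0.357. The chance is 95% with s = 0.5 and 52% with s = 0.9.

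These rates rest on two assumed inputs and on no displacement. They show sensitivity and are not estimates.

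**The case against.** The strongest reply is that the article never says the outcome includes UDCA. Total BA appears only in the eligibility text, the outcome list says serum BA, and no assay is named. That stands, so the point must be conditional on the assay. It does not dissolve the point, because the article says UDCA is a bile acid, uses routine laboratories and defines no exclusion.

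Second, the Background speaks of displacement and not simple addition, so the measured value may rise little or not at all. That also stands, and no difference in μmol/L can be claimed from the documents.

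Third, a reader might infer from the wash-out that the protocol itself regards on-UDCA values as unusable. The stated purpose is to obtain baseline data and confirm eligibility, and a wash-out also removes a treatment effect. The inference is not supported.

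Fourth, a reader might expect the problem to pass into the planned meta-analysis with the earlier placebo-controlled UDCA trial. The Background describes that work as sizing a later trial of perinatal morbidity and mortality and does not mention BA there.

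Fifth, the hypothesis covers several markers, and nothing says that BA alone decides it. This is correct. But nothing says that BA alone is insufficient either, and BA is named first.

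Finally, serum BA is the disorder's marker and is linked to fetal risk, so dropping it would be a real loss. That is accepted: the remedy should limit the claim and not remove the outcome.

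**Conclusion.** The concern holds conditionally. Unless the assay excludes UDCA, on-treatment serial and peak BA, and possibly cord BA, include some study drug in the UDCA arm, and counting it favours rifampicin. The planned sampling rules and off-drug baseline reduce this without removing it under continued daily dosing.

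The size cannot be derived from the documents. It depends on the UDCA share at trough, the degree of displacement, and how many women in the rifampicin arm receive UDCA as well. The figures above are illustrations; those without displacement are upper bounds for the assumed share.

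The documents do not support a stronger reading, that the BA comparison is known to be false by a given amount or that hypothesis 2 would be declared met on BA alone. Neither the pruritus outcome nor the transaminase result is affected by this counting. The point is still worth acting on, because it limits a conclusion that the trial could otherwise draw.

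**What to change.** - Keep serial, peak and cord BA as reported outcomes, each with the caveat that values on UDCA may include the drug. Name the assay and say whether it counts UDCA.
- State that a between-arm difference in unfractionated BA will not by itself count as meeting secondary hypothesis 2.
- Rest that hypothesis on listed markers not subject to this counting: transaminase, with bilirubin alongside. Note in the interpretation that ALT also triggers withholding of rifampicin, so treatment in one arm depends on that marker.
- Make a between-arm BA claim only on non-UDCA bile acids, where stored serum collected with consent under the separate protocols allows fractionation.
- Add a sensitivity analysis restricted to samples taken before any add-on drug. It addresses UDCA in the rifampicin arm and does not cure the counting in the UDCA arm.

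The cost is wording and a small amount of analysis. Fractionation is optional and depends on samples that may not exist for every woman. The downside is that one secondary claim becomes narrower.
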